**Figure 2 figure2:**
[figure not shown]
The study protocol showing the 5 steps for each participant, the planned evaluations, and the number of participants and dropouts.

### Preliminary Experiences with Online Questionnaires and Study Platform

The questionnaires in this study are very comprehensive (more than 100 items) and contain questions referring to medical data. Participants are also asked about the experience, acceptance, and usability of the study platform. The data collected from the first study survey (n=138) are displayed in Figure 3. The overall acceptance of the questionnaires was good, and most (62% *yes* and 29% *rather yes*) of the participants found the questions easy to understand (Figure 3 a), while 78% (48% *yes* and 30% *rather yes*) found them easy to answer (Figure 3 b). Almost all participants (80% *yes* and 16% *rather yes*) had no problems with the technical aspects of the study (Figure 3 c). When asked if the questionnaire was too time consuming, an equal number of participants (43%) answered with *yes* or *rather yes*, compared to participants who answered with *no* or *rather not* (Figure 3 d). Most (58% *yes* and 26% *rather yes*) of the participants felt that the directions and explanations were satisfactory (Figure 3 e), and the support of the study team was adequate for most (44% *yes* and 21% *rather yes*) of the participants (Figure 3 f). Many participants never contacted the study team (apart from study registration), resulting in 34% of the participants rating this aspect as *undecided*.

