## Methods

### Study Design

This is a prospective, longitudinal, and observational cohort study of cancer patients with four cohorts: (1) omnivore diet, (2) lacto-ovo-vegetarian diet, (3) vegan diet, and (4) other diets (see Table 1). All four cohorts will complete online questionnaires including a baseline assessment and follow-up assessments at 3 and 6 months (Figure 2). At the 12 and 24 month time points, participants will be contacted via email to complete a truncated study questionnaire.

**Table 1 table1:** Definition of dietary patterns.

Cohort	Meat & fish	Milk & dairy products	Eggs	Honey	Plant products
Omnivore diet	+	+	+	+	+
Lacto-ovo-vegetarian diet	-	+	+	+	+
Vegan diet	-	-	-	-	+
Other diets	Those that do not correspond to any of the above				

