### Study Population and Setting

Whenever possible, participants selected one of three defined diets (omnivore, lacto-ovo-vegetarian, or vegan) at baseline. If none of these diets was applicable, participants were classified as having *other diets* (Table 1). Participants were instructed to maintain the chosen diet for 6 months. In addition, respondents were encouraged to continue their prescribed cancer treatment during the study period, and to undergo all recommended follow-up investigations.

Calculation of the required sample size for this study is not possible, as the effect size of the dietary patterns is unknown. Therefore, this study is classified as a pilot study.

The study is being conducted online via a bilingual study website [27]. Registration processes, eligibility assessments, and questionnaires at baseline and follow-ups are all completed online between April, 2015 and December, 2016. Prior to study participation, potential participants performed an online eligibility check (Multimedia Appendix 1), and were asked to provide contact information and a signed patient information and consent form. After registration, participants received an email including their personal login information for the study website, their study identification number, and a link to their baseline questionnaire. Invitations for assessments at 3, 6, 12, and 24 months are delivered by email (Figure 2). If participants do not fill in their questionnaires at the respected time, they are sent reminder emails. In addition to the three main study questionnaires, study participants are asked to report any severe deterioration, unplanned change of their selected diet, or withdrawal from study participation, via online forms (Multimedia Appendix 2).

Ethical approval was obtained from the Ethics Committee of the City of Vienna on February 2nd, 2015 (EK 15-021-VK_NZ).

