### Measures and Evaluation Procedures

The primary outcome of this study is defined as complete tumor remission, and calculated as the rate of complete remissions at 6 months by intention-to-treat (ITT) analysis.

Secondary outcomes include tumor history, further classifications of tumor behavior (complete remission, partial remission, no change, or progression), relapse-free time (in months), survival rates for end stages, previous and current tumor therapies (including tolerance and side effects), comorbidities (eg, high blood pressure, stroke), as well as medications unrelated to the tumor (including dosage and intake plan). The determination of tumor behavior during the study period will be evaluated by two investigators, each using independent radiological and laboratory reports.

Data regarding previous nutritional history, the chosen diet during study participation, acceptance and feasibility of the chosen diet, frequency of dietary pattern change, extent and duration of nutritional changes, and the type and strength of support for nutritional changes will also be assessed. In addition, during baseline and follow-up surveys, adherence to dietary patterns will be cross-referenced by food frequency questionnaires (FFQs), which were specifically adopted for discrimination of plant- and animal-derived foods. Participants were also asked to self-report any unplanned change in diet during study participation. Nutritional status of participants will be evaluated using body weight (kg), BMI (kg/m^2^), laboratory test results (eg, albumin), and questions referring to eating problems. Results referring to nutrition and dietary patterns will be evaluated in terms of change and duration of change in dietary patterns (in months).

Study questionnaires also contain questions referring to quality of life covering the Karnofsky Index, as well as additional dimensions (ie, psychosocial wellbeing, psychosocial support). Online questionnaires were designed to be self-instructive and self-evident (Multimedia Appendix 3). In order to evaluate these parameters, questions pertaining to the study platform and interaction with the study team were also included in the questionnaires. The list of parameters included in the study questionnaire was designed to examine all study objectives, and is detailed in Multimedia Appendix 4.

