### Bias

This study was performed under free-living conditions, and it was not blinded (open-label design). Study participants chose their dietary pattern by themselves, resulting in participants and study team members being aware of the participants’ dietary pattern. This factor could introduce performance bias (systematic differences between groups in the care that is provided, or due to exposure to factors other than the factor of interest). When choosing their dietary pattern, participants were not manipulated in any way to choose a certain group, and we did not declare the vegan diet as a sufficient treatment for cancer, which might have led to exaggerated expectations.

As of July, 2016, 10 participants with cancer diagnosis and treatment were recruited via a clinical practice, and agreed to participate in the control group (unchanged omnivore diet). These participants have personal contact with study team members, unlike the rest of the included participants. However, all four groups (omnivore, lacto-ovo-vegetarian, vegan, or other) received the same neutral recommendations for avoiding malnutrition.

We did not exclude certain cancer types or stages, and cannot exclude a bias towards certain cancer types prior to the onset of the study. The distribution of these factors (frequency of certain types and stages of cancer) will be analyzed in the complete study evaluation.

Participants were recruited from various countries, and we considered socioeconomic and gender aspects in our study websites, newsletters, questionnaires, and dietary recommendations. Finally, a possible limitation of a web-based study is the attrition phenomenon, which leads to attrition bias. We aimed to minimize this effect using email reminders, and by offering frequent newsletters, blogposts, articles, and a Facebook site for the study.

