## Appendix

Multimedia Appendix 1 The checklist, which serves for potential participants to check their eligibility.

Multimedia Appendix 2 The login area, which can be accessed by the participant via a username and password. Participants can check their study status, fill out forms for unplanned changes in diet or health status, withdraw from the study, or upload new medical reports.

Multimedia Appendix 3 Example page from study questionnaire one demonstrating guidance of users with predefined answer options.

Multimedia Appendix 4 Data obtained at baseline and follow-ups (months 3 and 6).

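### The 6-month primary outcome depends in practice on a chain of long surveys with 32.7% completion, and no short outcome-only contact is planned at that time point

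*Protocol article*

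**What the plan says.** Under Measures and Evaluation Procedures the primary outcome is complete tumor remission, "calculated as the rate of complete remissions at 6 months by intention-to-treat (ITT) analysis". The same section gives the source of the tumor classification: "The determination of tumor behavior during the study period will be evaluated by two investigators, each using independent radiological and laboratory reports". The Appendix describes a login area, separate from the questionnaires, where participants can "withdraw from the study, or upload new medical reports".

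Study Design sets main assessments at baseline, 3 months and 6 months. Only for months 12 and 24 does it say that "participants will be contacted via email to complete a truncated study questionnaire". On the length of the main instruments, the Results state: "The questionnaires in this study are very comprehensive (more than 100 items) and contain questions referring to medical data".

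For non-response, Study Population and Setting says: "If participants do not fill in their questionnaires at the respected time, they are sent reminder emails". The Bias section acknowledges attrition bias and says "We aimed to minimize this effect using email reminders", together with newsletters, blog posts, articles and a Facebook site.

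Recruitment and Dropout Rates gives the position in May 2016. The first survey was completed by 138 of 242 and the second by 72 of 109. The third was sent to 43 people who had completed both earlier surveys and was completed by 33. The completers rate among the 101 enrolled at least 6 months earlier is given as 32.7%.

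**The concern.** An intention-to-treat remission rate needs a tumor status at 6 months for everyone in the cohort, not only for those who kept filling in questionnaires. The status itself needs little from the participant, because investigators judge it from medical reports and an upload route exists. Yet the only active follow-up described up to month 6 is the series of long surveys, and by the reported figures someone who missed an earlier one was not among those sent the 6-month survey. A non-responder is reminded of the same long form. The lighter instrument comes only after the primary time point.

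At stake is how much the primary rate, and any comparison between self-selected diet groups, can say. With most of the cohort lacking a 6-month survey, the result could be driven by who stayed, and staying may well be related to both diet choice and disease course.

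**Working it through.** **Inputs** (Recruitment and Dropout Rates, May 2016): completion 138/242, 72/109 and 33/43; 101 enrolled at least 6 months earlier; 33 completers; four deaths reported.

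**1. Reproduce the article's figure.** 33/101 = 32.7%, as stated. Non-completers: 101 − 33 = 68, and 68/101 = 67.3%. The Discussion prints this percentage beside the fraction 67/101, which is 66.3%, so the numerator is off by one. The 6-month percentages of 2% and 21% likewise need the denominator 43 (1/43 and 9/43), not the printed 33.

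**2. Cross-check by stage.** 138/242 = 57.0%; 72/109 = 66.1%; 33/43 = 76.7%. Product: 0.570 × 0.661 × 0.767 = 28.9% retained, of the same order as 32.7%.

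**3. Where the loss arises.** Taking the 43 as part of the 101 (an assumption), 101 − 43 = 58 were lost before the 6-month survey was sent and 43 − 33 = 10 at that survey. Shares of the 68: 58/68 = 85% and 10/68 = 15%. A shorter form sent only to the 43 could therefore raise completion to at most 43/101 = 42.6%. Any useful remedy has to reach the other 58.

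**4. What the missing data allow.** Let x of the 33 completers be in complete remission. If the other 68 have no status:
- lower bound = x/101
- upper bound = (x + 68)/101
- width = 68/101 = 67 points, whatever x is

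For illustration, x = 16.5 (50%, assumed) gives 16.5/101 = 16% to 84.5/101 = 84%. The width shrinks for every non-completer who supplied reports or whose outcome is otherwise known. For example, if all four deaths fell among the 68 and counted as no remission, it would be 64/101 = 63 points.

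**5. What a short form to all 68 might recover.** The documents give no response rate, so this is a range of assumptions:

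| Assumed response | Outcomes | Still missing | Width of bounds |
|---|---|---|---|
| 0% | 33 | 68 | 67 points |
| 25% | 33 + 17 = 50 | 51 | 51/101 = 50 points |
| 50% | 33 + 34 = 67 | 34 | 34/101 = 34 points |

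**The case against.** A reader might infer that the long 6-month questionnaire causes the loss of two thirds of primary outcomes and that this loss is avoidable. The article does not support that reading, for four reasons.

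- **Stage.** Completion was highest at the 6-month survey (77%), and by step 3 only about 10 of the 68 losses arose there. Those 43 people had already completed two long surveys, so 77% does not show that length is harmless, but it does not show harm either.
- **Cause.** The Discussion attributes attrition to the anonymous setting and the absence of contact with the team. It argues that far more people left between surveys than left one unfinished. That is an inference with no comparison behind it, and someone who has met a long form once may not open the next. Burden is therefore not excluded, but no data tie dropout to length.
- **Ratings.** In the first-survey data (n=138), 43% found the questionnaire too time consuming and an equal 43% did not. The 138 matches the number who completed that survey, so people who never finished it are apparently not represented. The figure can be cited in neither direction for the 6-month form.
- **Survey versus outcome.** Not completing a survey is not the same as having no remission status, because reports can be uploaded separately. How many non-completers did so is not stated. Dropouts also include deaths and withdrawals, which no further form recovers.

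It is also fair that this is a declared pilot that sets out to test its platform and openly names attrition bias. These points remove the causal claim and any firm estimate of benefit. They do not answer the narrower point: no low-burden request for the primary outcome is described at month 6. If lack of contact is the true cause, such a request is still a sensible response.

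**Conclusion.** The point holds as a cheap improvement, not as proof of an avoidable loss. The primary outcome relies in practice on a sequence of long surveys that 33 of 101 participants completed (32.7%). The stated countermeasures leave the task unchanged, and the truncated form is not used at the primary time point.

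The 67-point width of the worst-case bounds assumes that none of the 68 non-completers supplied reports or has a status known in another way; to the extent that they did, the problem is smaller. The split of 58 and 10 assumes that the 43 belong to the 101. All figures are interim. The share that a short form would recover cannot be derived from the article; 25 to 50% is an assumption that shows the scale only.

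**What to change.** Amend Study Population and Setting as follows. At month 6, every registrant who has not withdrawn and has not completed the full 6-month survey is sent a short outcome-only form, whether or not earlier surveys were completed. The form asks for tumor status with report upload, current diet, weight and vital status. State that it supplies the primary outcome where the full survey is missing, that the source is recorded for each participant, and that a sensitivity analysis by source is run.

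The cost is small: one more automated contact and a short form. The truncated month-12 and month-24 questionnaire may serve as its basis, but its content is not shown, so some adaptation may be needed. Secondary items stay missing for these participants, and primary outcomes then come from two forms. If registration counts as enrolment, 242 − 101 = 141 registrants had not yet reached month 6 in May 2016, and data collection ran to December 2016, so the change could still have applied to them.

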**Figure 3 figure3:**
[figure not shown]
The participants’ opinions about data surveys (n=138).

## Discussion

The purpose of this study is to assess whether a reduction or elimination of animal proteins from the diet influences the course of existing cancer, and if this tactic can increase remission rates while following standard oncological therapy. Data is being collected using online data surveys.

### Study Aims and Approach

To date, only a small number of studies have investigated the effect of nutrition on established cancer. Among these studies, research on CRC, prostate cancer, and breast cancer have given insights regarding the impact of animal proteins on cancer [16,18,20,21]. McCullough et al found higher CRC-specific mortality in patients with consistently high intake of red and processed meat pre- and post-diagnosis, in comparison to those who did not [20]. Interestingly, the difference was not significant if red and processed meat intake were calculated separately. This result could indicate the significance of the total amount of animal proteins and the importance of defining food patterns. This study did not examine a group without meat consumption, possibly reducing the effect size on CRC-related mortality [20].

Richman et al reported that the post-diagnostic consumption of processed and unprocessed red meat, fish, or skinless poultry was not associated with prostate cancer recurrence, whereas consumption of eggs and poultry with skin may increase the risk of recurrence [21]. The FFQ used in this study included 137 food and beverage items and supplements, from which the research team selected five food groups (processed red meat, unprocessed red meat, fish, poultry, and eggs) but did not include dairy products in their analysis. Current research suggests that the intake of dairy products is linked to prostate cancer [32,33], and this finding may have affected patient cancer recurrence rates in the Richman et al study. In another study, researchers observed that men with a high post-diagnostic cruciferous vegetable intake had a statistically significant (59%) decreased risk of prostate cancer progression compared to men in the lowest quartile [34].

It has been demonstrated that breast cancer patients who consumed high levels of soy products had cancer recurrence rates equal to (and in some cases even less than) patients with low consumption [16,18], but it was not reported whether the patients consumed meat, fish, eggs, or milk, and in what quantities. Similarly, Pierce et al reported that breast cancer patients who continued consuming meat, but increased their intake of fruits and vegetables to five portions per day and physical activity to six times per week, had increased survival rates by as much as four fold, in comparison to the lowest intake and physical activity cohort [35].

Animal proteins have been reported to play a significant role in certain cancer types, such as hepatocellular carcinoma of hepatitis-induced carcinoma [36], and may also be a factor in many other cancer types [37-40]. This study aims to approach all cancer types in the pilot study. In addition, we will not examine single foods or food groups, but instead investigate whole dietary patterns. As we divide our study collective into four cohorts (omnivore, lacto-ovo-vegetarian, vegan, or other), we hope to draw correlations between the amount of consumed animal proteins and cancer progression and survival.

This study will make it possible, for the first time, to estimate the effect size of animal protein consumption in cancer patients, and to stratify for age, body weight, tumor stage, and tumor type. These findings may be of high importance for the selection of certain patient groups for future studies with more detailed questioning.

It is known that dietary advice is difficult to follow for many patients, making it challenging to achieve improved prognoses by dietary advice alone [22,23]. Therefore, it is crucial to examine the acceptance and feasibility of the recommended diet. To this end, tools are needed that can increase motivation and compliance, and reduce attrition rates. Online tools like ours appear to be particularly suitable for this issue, based on a study that used a similar procedure [24].

Changing one’s diet to a more plant-based diet has not only been shown to decrease the negative side effects of chemotherapy in cancer patients [6] (such as the severity of vasomotor symptoms [41] and events of hot flush (HF) in HF-positive women recently treated for breast cancer [42]) but also to regulate weight [12], which plays an important role in the outcome of cancer treatments [43,44]. Suggestions that a vegan diet might lead to deterioration have not be empirically proven [45], and intermediate fasting did not have detrimental effects on patients receiving chemotherapy for hematological diseases [46,47].

Self-reported measures have been frequently used and analyzed in psychological studies in recent years [48], but not as extensively in clinical studies. In the context of this study, we developed and tested an Internet study platform, which enabled us to reach a wider population by decreasing the threshold of participation for patients. In addition, the expenditures for both the study team and the patients are clearly decreased. We hope to use the current study to adapt and optimize the portal for future investigations, including study questionnaires and data-collecting processes. The current study platform may allow for more economical and more precise studies regarding the effects of nutrition on existing cancer.

In contrast to statements that self-reported and online-collected data show less validity, publications exist that demonstrate the opposite [25,49,50]. These new technologies have the potential to increase data precision, quality, and quantity [25,49,50], particularly if the technology of this study platform is integrated with tools for precise dietary monitoring in the future.

### Preliminary Experiences

The preliminary dropout rate of 67.3% (67/101) appears to be quite high. However, this rate is comparable with other studies performed online, in which dropout rates range from 33% [49] and 34% [51], up to 82% [52] and 88% [53], depending largely on the type of study and if participation was associated with clinical contact and intervention. Dropout rates are also influenced by the disease and stage being investigated.

The questionnaires in this study are very comprehensive (more than 100 items) and contain not only personal questions about symptoms and habits, but also questions referring to medical data. It was important to evaluate whether or not participants were able to complete the surveys. The answers regarding experience and usability of the study platform and questionnaires were encouraging, and the majority of participants did not experience difficulties. This notion is supported by the fact that many more registered participants dropped out between the three study surveys than those who left an incomplete questionnaire. Dropout rate was highest after the first data survey and decreased significantly with each subsequent survey. We therefore conclude that anonymity and lack of contact with the study team caused the attrition rates.

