### Recruitment and Dropout Rates – Preliminary Experiences

As of May, 2016, 530 participants filled out the checklist and 242 (45.7%) have registered for the study. Most respondents were female (174/242, 71.9%), while 68 were male (28.1%). Mean age was 54.7 years (standard deviation 11.7). Most participants were recruited in German speaking countries (Germany, Austria, and Switzerland). As shown in Figure 1, most participants found the website via the Internet or social media (eg, Facebook and Twitter).

Dropouts occurred at each stage of the study, from the checklist for eligibility to the third data survey, as shown in Figure 2. After filling out the registration forms, 242 participants received the invitation for their first data survey, which was completed by 138 respondents (57.0%). Some respondents (33/242, 13.6%) sent an incomplete survey, and 68 of the original participants (28.1%) did not send a survey. Dropout rates consider participants who withdrew study participation, died, or did not answer after being reminded by email. Four patients have been reported to have died as of May, 2016.

Three months after completing the first survey, participants received an invitation for the second survey (n=109 as of May, 2016), which was completed by 72 respondents (66.1%). Four participants (4/109, 3.6%) sent an incomplete survey and 33 (30.3%) dropped out of the study at this point. The study is still underway, and participants who did not receive the second and/or third surveys have been excluded from these calculations.

The 6-month data survey was sent to 43 participants who completed the first and second surveys. As of May, 2016, this survey was completed by 33 participants (77%); 2% (1/33) sent an incomplete survey, and 21% (9/33) dropped out of the study at this point. Given the number of participants who enrolled in the study at least 6 months before May, 2016 (n=101), this gives a completers rate of 32.7%.

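### The article's counts do not show a significant fall in dropout at each survey, and the cause of attrition inferred from that fall was not tested

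*Protocol article*

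**What the plan says.** The Discussion (*Preliminary Experiences*) opens its account of attrition with "The preliminary dropout rate of 67.3% (67/101) appears to be quite high". It then describes the pattern over time, "Dropout rate was highest after the first data survey and decreased significantly with each subsequent survey", and goes straight on to a cause: "We therefore conclude that anonymity and lack of contact with the study team caused the attrition rates".

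The counts are in the Results (*Recruitment and Dropout Rates – Preliminary Experiences*), as of May 2016. Of 242 people invited to the first survey, 138 completed it; for the rest, "Some respondents (33/242, 13.6%) sent an incomplete survey, and 68 of the original participants (28.1%) did not send a survey". The term is defined there: "Dropout rates consider participants who withdrew study participation, died, or did not answer after being reminded by email". Of 109 invited to the second survey, 72 completed it, 4 sent it incomplete and 33 dropped out. The third survey went to 43 people who had completed both earlier ones. Of these, 33 completed it and "2% (1/33) sent an incomplete survey, and 21% (9/33) dropped out of the study at this point". Completion is given as 32.7% of the 101 people enrolled at least six months earlier.

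*Statistical Analyses* sets P<0.05 as the meaning of significant. No test or P value accompanies the statement about falling dropout.

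**The concern.** A claim of significance is made without a test, beside counts from which a reader can check it. On the article's own definition, the first of the two steps goes up. The next sentence begins with *therefore* and names a cause, so the causal statement leans on a pattern that the counts do not show.

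Testing the online platform is a stated objective (end of the *Introduction*), and *Online Platform Performance* lists dropout between and within questionnaires as one of its measures. The Discussion plans to adapt the portal for later studies. If lack of contact is taken as the established cause, that redesign may aim at contact and overlook other explanations, such as the length of the questionnaire.

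**Working it through.** **1. Printed figures.** Most reproduce: 138/242 = 57.0%, 33/242 = 13.6%, 68/242 = 28.1%, 72/109 = 66.1%, 33/109 = 30.3%, 33/43 = 77%, 33/101 = 32.7%. Three fractions do not match the percentage beside them:

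- 67/101 = 66.3%, but 67.3% is printed. Non-completers are 101 − 33 = 68, and 68/101 = 67.3%.
- 1/33 = 3.0%, but 2% is printed; 1/43 = 2.3%.
- 9/33 = 27.3%, but 21% is printed; 9/43 = 20.9%. The denominator is confirmed by 33 + 1 + 9 = 43.

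In each case the percentage is right and the fraction is misprinted. (4/109 is 3.67%, printed as 3.6%, which is only rounding.)

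**2. Rates by survey, two ways of counting.** Non-completion is the number invited minus the number completed: 242 − 138 = 104, 109 − 72 = 37, 43 − 33 = 10.

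| Survey | Invited | Dropout as defined | All non-completion |
|---|---|---|---|
| 1 | 242 | 68 (28.1%) | 104 (43.0%) |
| 2 | 109 | 33 (30.3%) | 37 (33.9%) |
| 3 | 43 | 9 (20.9%) | 10 (23.3%) |

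**3. Each step.** Fisher's exact test on the 2×2 table of adjacent surveys:

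- Dropout as defined: 28.1% to 30.3%, p=0.70; 30.3% to 20.9%, p=0.32.
- All non-completion: 43.0% to 33.9%, p=0.13; 33.9% to 23.3%, p=0.24.

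The uncorrected chi-square test agrees (p=0.68 and 0.25; 0.11 and 0.20). As a check by hand on the first pair, z = (p₁ − p₂)/√[p(1 − p)(1/n₁ + 1/n₂)] with p = 101/351 = 0.288 gives −0.0218/0.0522 = −0.42, so p=0.68.

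**4. Overall trend.** Cochran-Armitage with scores s = 0, 1, 2: T = Σ s(x − np) and V = p(1 − p)[Σ ns² − (Σ ns)²/N], with N = 394. The bracket is 281 − 195²/394 = 184.5.

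- Dropout as defined: p = 110/394 = 0.279, T = −3.44, V = 37.1, z = −0.56, p=0.57.
- All non-completion: p = 151/394 = 0.383, T = −17.7, V = 43.6, z = −2.69, p=0.007.

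These tests treat the surveys as independent samples. They are not: the later groups are drawn from the earlier ones. The p-values are therefore approximate.

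**5. The causal step.** A sequence of rates does not identify a cause. That would need at least a comparison of retention by level of contact, and none is reported. *Bias* mentions 10 participants recruited through a clinical practice who had personal contact, but gives no retention for them. The article also contains a competing explanation. The questionnaires have more than 100 items, and among first-survey respondents (n=138) 43% found the questionnaire too time consuming or rather so, while an equal 43% did not.

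**The case against.** The strongest defence is that the direction is right. The headline 67.3% counts every non-completer, and on that count the rates fall throughout, with a significant overall trend; equivalently, printed completion rises from 57.0% to 66.1% to 77%. This stands, so a reader should not infer that the downward pattern is simply false. What fails is the claim of a significant fall at each step. Part of the fall may also be selection, because each later survey went to people who had already stayed in.

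*After the first data survey* could mean loss between surveys 1 and 2. Then *highest* is correct (30.3%), but only one later step remains, to 20.9% (p=0.32). *Significantly* might also be meant loosely, but the article defines the word by P<0.05, and on its own definition of dropout the step from survey 1 to survey 2 is upward.

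Four stronger readings are tempting, and the document does not support them:

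- *The attrition figures in general fail to reproduce.* Most do, including the 32.7% that a later study would use.
- *The feasibility conclusion falls.* Feasibility is assessed by diet compliance, reported diet changes and questionnaire items, and the platform verdict draws largely on usability answers. Only the stated cause of attrition is affected.
- *Three registrants are lost.* The first-survey counts sum to 138 + 33 + 68 = 239 of 242, but Figure 2, which gives participants and dropouts, is not shown here and may account for them.
- *Dropouts were never asked why.* There is an online withdrawal form whose content is not visible.

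It is also fair to say that these are interim counts, and that the Discussion itself names other influences on dropout, such as study type, clinical contact, disease and stage.

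**Conclusion.** The point holds in limited form. On neither the article's definition of dropout nor a count of all non-completers is there a significant decrease at each survey: the smallest step-wise Fisher p-value among these four comparisons is 0.13. Counting all non-completers does show an overall decline, from 43.0% to 23.3%, among increasingly selected participants. The causal conclusion does not follow on either count, because nothing reported compares participants by contact; it may be true, but it is untested here. The three fraction errors are misprints and leave overall attrition at about two thirds.

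This rests on the May 2016 counts as printed, on 43 as the third-survey denominator, and on tests that approximate by ignoring the overlap of participants. Severity is minor: eligibility, the primary outcome and its planned analysis do not depend on these sentences.

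**What to change.** In the Discussion, delete the statement of a significant decrease at each survey, or replace it with the counts, for example: *Non-completion among those invited was 104/242 (43.0%), 37/109 (33.9%) and 10/43 (23.3%) at the three surveys; it was lower at later surveys, which went to increasingly selected participants.* If dropout as defined is reported instead, give 68/242, 33/109 and 9/43, and say which count is used.

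Reword the causal sentence as a hypothesis that the study did not test. Set questionnaire burden beside it as an alternative, quoting both 43% figures.

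Correct 67/101 to 68/101 in the Discussion, and 1/33 and 9/33 to 1/43 and 9/43 in the Results. Leave the percentages beside them and the 32.7% as they are.

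The cost is a few lines of text; no new data or analysis is needed.
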